**Fig. 1 Fig1:**
[figure not shown]
Organization of retrospective study

For the prospective phase, a new cohort of 33 patients (11 with spontaneous Type 1 BrS pattern, 11 patients in whom ECG repolarization patterns in leads V1 and V2 are suggestive of disease and a type 1 BrS pattern induced by ajmaline/flecainide infusion, 11 with suspected tracings but negative after ajmaline/flecainide test) and 11 controls will be enrolled. At baseline, each subject will undergo a cardiological examination, an ECG recording and a venous blood sampling for transcriptomics and microvesicles analysis performed.

Subjects with either unequivocal spontaneous or pharmacologically induced ECG patterns diagnostic for Type 1 BrS will undergo electrophysiologic study (EPS) with Programmed Electrical Stimulation (PES); after 12 months a final cardiological control examination will be performed (Fig. 2).

**Fig. 2 Fig2:**
[figure not shown]
SPIRIT figure of retrospective and validation BrAID study

For the validation phase a new cohort of 100 patients, of which 30 control subjects and 70 subjects (35 spontaneous BrS and 35 suspected), will be enrolled and undergo the same clinical examinations of prospective phase (Fig. 2).

The studies will be performed following the Declaration of Helsinki; they were already approved by the Comitato Etico Area Vasta Nord Ovest, Pisa, Italy. Blood tests and analyses will follow the guidelines of the Human Tissue Act (2004). The trial was registered in ClinicalTrials.gov (Identifier: NCT04641585).

### ECG

For the prospective and the validation studies, 12-lead ECG with standard recording parameters (speed paper 25 mm/s, amplification of 10 mm/mV, sampling rate 10 s at 500 Hz, filters: 0.5–100 Hz) will be acquired and the following parameters analyzed by the cardiologist: PQ interval, QRS duration, QTc interval, the presence of a Type 1 BrS pattern [25], the presence of depolarization abnormalities (major: epsilon waves; minor: terminal activation duration [TAD] ≥ 55 ms) and repolarization abnormalities (major or minor T-wave inversions) [26].

### Transcriptomics and microvesicles extraction

Whole blood will be collected in PAXgene blood RNA system tubes (DIALAB ITALIA Srl, Milan, Italy), containing reagents used to stabilize RNA immediately. This method efficiently stabilizes the intracellular RNA, preserves the sample at temperatures between − 20 and − 80 °C and allows the maintenance of the same degree of fresh blood purity. Plasma samples will be collected in polypropylene tubes containing K3 EDTA, quickly separated by centrifugation at 1500 g for 15 min at 4 °C and stored in 500 μl aliquots while serum samples will be collected in dedicated tubes (without anticoagulant) centrifuged for 15 min at 1000 g and stored at − 20 °C until use.

Total RNA will be extracted from samples collected in PAXgene tubes using a dedicated kit (PAXgene blood RNA Kit, Qiagen, Milan, Italy). Total microvesicles will be isolated from serum or plasma samples using dedicated high-efficiency kits. The miRNAs will be isolated from both blood samples and microvesicles by specific assays. All RNA samples will be stored at − 80 °C after evaluation of integrity, purity and concentration.

RNA-seq will be run using NextSeq. 500 (Illumina, San Diego, California, United States) for next-generation sequencing. The library will be prepared following the TruSeq Stranded mRNA LT kit (Illumina) protocol. Libraries will be quantified using the Qubit 2.0 fluorometer (Invitrogen, Life Technologies, Grand Island, NY) and the dimensional profile will be analyzed on the 2200 TapeStation instrument (Agilent Technologies, Santa Clara, CA).

miRNA analysis will be performed in microvesicles, and the small RNA libraries will be generated with the TruSeq Small RNA Library Preparation Kit (Illumina). Sequencing will be performed on the NextSeq 500 system (Illumina).

### Electrophysiologic study and programmed electrical stimulation (PES)

Patients with spontaneous or suspected BrS will undergo PES to assess the inducibility of ventricular tachycardia (VT) or fibrillation (VF). In according to the internationally recognized guidelines [27], PES will be performed by a cardiologist with full training in the electrophysiologic study, supported by a dedicated nurse, in the Electrophysiology Laboratory, equipped with fluoroscopy, instrumentation for recording ECG and hemodynamic signals, and equipment for resuscitation. PES will be carried out with two drive cycles (600 and 400 ms) and up to two extra stimuli [28]. The inducibility protocol would be performed from the right ventricular apex and the right ventricular outflow tract unless ventricular tachycardia was already induced at the first location.

### Ajmaline/flecainide test

These tests will be performed and interpreted by experienced cardiologists with expertise in evaluating and managing inherited cardiac conditions, with advanced cardiovascular resuscitation equipment facility. An antecubital vein will be cannulated and a continuous 12-lead ECG monitoring performed. Baseline 12 lead ECGs will be recorded after a period of rest. The ECGs and blood pressure will be assessed at 1 min intervals throughout the test. Ajmaline at a dose of 1 mg/kg will be intravenously administered as a phased infusion over 10 min [29]. For the flecainide test, the drug will be administered according to published data [30] (2 mg/kg i.v. bolus over 10 min).

The infusion will be interrupted when the ECGs becomes diagnostic with typical Type 1 BrS pattern, or the QRS duration increased by 130% or more [25]. ECGs will be monitored until the PR interval, and QRS durations are normalized. The test is considered positive if J point elevation of ≥ 2 mms with coved ST elevation in one or more right precordial leads will be recorded [31].

### Outcome measures

Primary outcomeThe primary outcome of the BrAID study is the percentage of identification of Type 1 BrS ECG pattern with ML models compared to the diagnosis made by expert Cardiologists. Data will be obtained by the analysis of entire 12-leads ECG time series in terms of heart rate (HR), QRS interval duration, complex repolarization shape and ECG features associated with the syndrome (coved ST, QRS fragmentation, ST-segment depression, negative T wave, J wave amplitude ≥ 2 mm, broad P wave with some PQ prolongation) by the neural network in a cohort of 44 patients (prospective study) and validated in a cohort of 100 patients (validation study).Secondary outcomesTwo secondary outcomes of BrAID study are: (1) the identification of biomarkers associated with Type 1 Brugada Syndrome by means of blood transcriptomic profile and microvesicles analysis of patients; (2) the development of a stratification risk system for Type 1 Brugada Syndrome by the integration of ECG Machine Learning algorithms, clinical data and biomarkers.

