## Methods/design

### Study design and population

The study is multicentric, non-randomized and no-profit. Patients with BrS will be enrolled at Fondazione Toscana Gabriele Monasterio, U.O.C. Cardiologia Ospedale San Donato, Azienda Usl Toscana Nord Ovest U.O.C. Cardiologia Ospedale Versilia, Azienda Ospedaliera Universitaria Careggi SOD Aritmologia, Azienda Ospedaliero Universitaria Pisana Cardiologia 2 U.O.C. Cisanello.

The protocol recognizes three phases: retrospective, prospective and validation studies. The prospective and validation studies' enrolment duration will be 24 months and will start during January 2021.

The ECG diagnosis of BrS will be strictly based on the recommendations of the 2015 European Society of Cardiology guidelines for the management of patients with ventricular arrhythmias and the prevention of SCD [2]. Inclusion criteria for BrS patients enrolment, both for the prospective and the validation study, are represented by Type 1 BrS (Coved) electrocardiographic changes, either spontaneous or induced by ajmaline/flecainide test [24, 25] or in the presence of high clinical suspicion (familiarity for BrS, patients who survived cardiac arrest with no apparent cause); age between 14 and 65 years. The control group will be represented by subjects of comparable age who undergo a cardiological examination as outpatients and present a normal baseline ECG. The presence of structural cardiac disease or concomitant diseases that may impair the completion of the protocol, lack of informed consent, pregnancy, history of coronary artery disease, severe renal or hepatic insufficiency will represent the exclusion criteria. Structural heart disease will be excluded in all patients before enrolment by non-invasive imaging (echocardiography and/or cardiac MRI).

The retrospective study aims to train the Machine Learning algorithms for BrS ECG patterns recognition; the prospective study is finalized to collect blood samples for disease-associated biomarkers by transcriptomic and microvesicles analysis, refine the ECG ML algorithm previously developed and integrate this data in the risk stratification algorithm; the validation phase will test the biomarkers discovered in the prospective study, the ECG ML algorithms and the stratification risk in a new cohort of patients.

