### Statistical analysis

For the sample calculation, reference will be made to compare sequenced RNAs, using a two-tailed Student's test for independent data. Considering the technology used to obtain RNA data [32], an expression variation of 6 (fold change) being expected, and assuming a gene coverage depth of 0.75 with a standard deviation of 1, a power of 80% and an alpha of 0.05 will be guaranteed by a sample of 11 subjects per group: 11 spontaneous BrS, 11 Suspected BrS (positive), 11 Suspected BrS (negative), 11 Control.

For bioinformatics analysis of transcriptomics, a case calling and demultiplexing will be performed raw processing data for both format conversion and demultiplexing by the Bcl2Fastq 2.20 version of the Illumina pipeline. Reads deduplication based on the unique molecular identifier (UMI) composed of 8 random bases for unambiguous identification of unique library molecules will discriminate between true PCR duplicates and independent adaptor ligation events to fragments with the same start site. DESeq2 will be used to perform comparisons between expression levels of genes and transcripts. Normalization will be performed using the median-of-ratios method [33]. An initial list of modulated genes in the current experimental set will be determined by applying a likelihood ratio test [34]. Adjusted *p*-value < 0.01 will be set an initial threshold. Further analyses on pairwise comparison will be obtained by filtration of the Fold Change (FC) calculation: the ratios between the relative expression values of two different conditions, expressed as the absolute value, will be assessed above 3.

Regarding the predictive models of Machine Learning, the sample numbers for the retrospective study (n = 300) and the final validation study (n = 100) correspond to the number of cases already classified by the clinical centers as Brugada syndrome, the former, and which can be collected during the experimental activities of the project by the same units, the latter. According to the activities foreseen in the trial, validation methodologies (cross-validation techniques) that will exploit this availability of data to develop and estimate the predictive models consistent with state of the art will be prepared [35].

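### The 44 prospective patients both refine the ECG algorithm and supply the primary outcome, and the plan does not clearly keep the 100 validation patients out of model development

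*Protocol article*

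**What the plan says.** The primary outcome (protocol article, Outcome measures) is "the percentage of identification of Type 1 BrS ECG pattern with ML models compared to the diagnosis made by expert Cardiologists". The same paragraph says the data will be obtained "by the neural network in a cohort of 44 patients (prospective study) and validated in a cohort of 100 patients (validation study".

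Study design and population gives each phase a role for the ECG model:

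- Retrospective: "The retrospective study aims to train the Machine Learning algorithms for BrS ECG patterns recognition".
- Prospective: "refine the ECG ML algorithm previously developed and integrate this data in the risk stratification algorithm".
- Validation: "the validation phase will test the biomarkers discovered in the prospective study, the ECG ML algorithms and the stratification risk in a new cohort". After Fig. 2 this cohort is again described as newly enrolled: "For the validation phase a new cohort of 100 patients". The Abstract also gives it a testing role.

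The machine-learning paragraph of Statistical analysis explains where the 300 and the 100 come from. Its next sentence says that cross-validation techniques will "exploit this availability of data to develop and estimate the predictive models". The 44 are not mentioned in that paragraph.

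**The concern.** A model adjusted with the help of a set of patients tends to look better on those patients than on others. If the headline percentage is read on the 44 after they have been used for refining, it describes fit to those patients and not recognition of the Type 1 pattern in the next patient. The only other place the outcome is read is the cohort of 100. Its value as an independent test depends on its staying untouched until the model is final, and the cross-validation sentence does not secure that.

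The stated purpose is a tool to help clinicians diagnose, so the primary figure is the one readers will carry away. The independence of the 100 cannot be restored once they have been used for tuning. The roles therefore need settling before any validation ECG is scored.

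**Working it through.** **1. The roles side by side**

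| Cohort | Study design and population | Outcome measures | Statistical analysis, ML paragraph |
|---|---|---|---|
| Retrospective, 300 | trains | not named | named just before the cross-validation sentence |
| Prospective, 44 | refines | supplies primary outcome data | not named |
| Validation, 100 | tests | validates | named just before the cross-validation sentence |

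The 44 hold a development role and a scoring role at once. The 100 are a pure test set in two columns. In the third they can be read as part of the data used to develop and estimate the models.

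**2. Is there a figure of the plan to reproduce?** No. The 44 is 4 × 11, sized for the RNA comparison. The 300 and the 100 are set by availability. No accuracy target is stated, so what follows is illustration under assumed inputs.

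**3. Optimism from choosing and scoring on the same patients.** Assume K = 20 candidate settings, all with true accuracy 0.85, the best one being reported on the data used to choose it.

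- Formula: inflation = E[max of 20 standard normals] × √(1 − ρ) × √(0.85 × 0.15 / n), with E[max] ≈ 1.87.
- n = 44: standard error √(0.1275/44) = 0.0538. Inflation is 10.1 points at ρ = 0 and, multiplying by √0.2 = 0.447, 4.5 points at ρ = 0.8.
- n = 100: standard error √(0.1275/100) = 0.0357. Inflation is 6.7 and 3.0 points. These two apply only if the 100 are themselves used for selection.

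Candidates scored on the same ECGs will be correlated, so the independent case is an extreme.

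**4. Optimism from refitting.** This is a small simulation with a ridge linear classifier and 10 to 40 features, all assumed. Ranges run from 10 to 40 features.

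| Use of data | Scored on the data used | On new patients | Gap |
|---|---|---|---|
| Refit on 300 + 44, score the 44 | 82.3% to 84.8% | 80.7% to 78.6% | about 2 to 6 points |
| Refit on the 44 alone, score the 44 | 87.5% to 99.9% | 75.8% to 62.5% | about 12 to 37 points |
| Fit on 300 + 100, re-score the 100 | 82.0% to 84.0% | 80.8% to 78.8% | about 1 to 5 points |

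Five-fold cross-validation on the pooled 300 + 100, scoring only held-out cases, gave 80.6% to 78.2% against a true 80.8% to 78.8%. That is no over-statement.

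**5. Precision if only the 100 are used.** At an observed 80%, the Wilson 95% interval is 71.1% to 86.7% with 100 patients. With 44 it is 66.0% to 89.2%.

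**The case against.** Three points on the other side have force.

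First, the order of events in the 44 is unstated. The model trained on the 300 could be scored on the 44 and only then updated. Both sections would then be satisfied and the figure would be clean. That is possible, but nothing in the article says so, and the wording equally allows scoring after refinement.

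Second, a reader might infer from the cross-validation sentence that the 100 are used in development, so that no cohort is left untouched. The document does not support that. The Abstract, Study design and population and Outcome measures all give the 100 a testing or validating role. The Statistical analysis section itself treats them as the final validation study, and its cross-validation sentence refers back to the activities foreseen in the trial. What stands is that the sentence can be read either way and sits badly with "the ECG ML algorithms and the stratification risk in a new cohort of patients".

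Third, a reader might conclude that accuracy is bound to be over-stated. It is not. Properly nested cross-validation is close to unbiased, as step 4 illustrates for held-out scoring, and a model locked before the 100 are scored would be unbiased too. Nor does the concern carry over to the biomarkers. They are discovered in the prospective study and tested in the validation cohort, and the retrospective cohort contributes ECG traces only.

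It can also be said that locking a model and fixing a threshold are details a condensed article may leave to the full protocol or analysis plan. That is fair, and their absence is not the complaint. The complaint is that the roles the article does assign do not fit together.

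**Conclusion.** The point holds as a conflict of roles. The 44 refine the algorithm and also supply primary outcome data, with no split and no order of scoring given, so a primary figure from the 44 may be over-stated. For the 100, the finding is one of unclear wording: the article does not plainly say that they stay out of development.

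The size cannot be derived from the document. Under best-of-20 selection at 85% true accuracy, it is about 4.5 to 10 points at n = 44. Under the assumed linear classifier, refitting on 300 + 44 gives about 2 to 6 points. Refitting on the 44 alone gives much more, but nothing in the article says the model would be refitted that way.

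**What to change.** Reconcile Study design and population, Outcome measures and Statistical analysis as follows:

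1. Estimate the primary outcome once, in the 100 validation patients only, with the model and its decision threshold locked before any of those ECGs is scored.
2. Confine cross-validation for development to the retrospective 300 and the prospective 44, and say so in the cross-validation sentence.
3. Remove the 44 from the definition of the primary outcome and report results in them as development performance.

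The cost is wording and a locked, dated copy of the model. There are two small downsides. The 100 cannot be used to improve the model until the primary result has been read, and precision rests on 100 patients, as step 5 of the working shows. The change should be made before validation ECGs are scored.

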## Background

Brugada Syndrome (BrS) is a hereditary arrhythmogenic disease with an electrocardiographic (ECG) pattern characterized by ST-segment elevation in the right precordial leads and burdened by the risk of sudden cardiac death [1]. The prevalence of the syndrome is estimated to be 15 per 10,000 in South East Asia, including Japan, and 2 per 10,000 in the Western countries. BrS has been considered responsible for 4–12% of all sudden deaths and up to 20% of sudden deaths in patients with structurally normal hearts. It is 8 to 10 times more prevalent in men than in women. In a recent meta-analysis, the incidence of arrhythmic events (sustained VT or VF or appropriate implantable cardioverter defibrillator (ICD) treatment or sudden death) in patients with Brugada syndrome was 13.5% per year in patients with a history of sudden cardiac arrest, 3.2% per year in patients with syncope and 1% per year in asymptomatic patients [2]. As more data become available, the currently accepted percentages of Sudden Cardiac Death (SCD) due to BrS need to be updated to establish the real incidence of the syndrome in unexpected deaths in different populations [3].

In these last years, the research interest on BrS has significantly increased since it prevalently affects healthy young adults during their most productive years [1]. Due to its genetic component, there is a need to identify other potentially affected relatives, focusing on children [4].

There are three types of ECG changes associated with Brugada Syndrome. Type 1 shows, in more than one right precordial lead, a coved shape of the ST-segment with J wave or ST-elevation of ≥ 2 mm (mV) at its peak followed by a negative T wave with little or no isoelectric interval; in Type 2, the ST segments have a high take-off but the J amplitude of ≥ 2 mV rises to a gradually descending ST-segment remaining ≥ 1 mV above the baseline followed by a positive or biphasic T wave; these abnormalities result in a saddle-back configuration. Finally, Type 3 presents ST elevation on the right precordial leads < 1 mm (saddle-back type or coved morphology).

From a diagnostic point of view, BrS can be confirmed in non-diagnostic cases by developing the peculiar ECG patterns in V1 and V2 after administration of Na + channel blockers (i.e., ajmaline, flecainide) [5].

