### Trial status

Participant recruitment will start in January 2021. The study completion will be in September 2023.

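### The stated completion date falls before the last 12-month visits, and 12-month arrhythmic events, if they are what the risk score predicts, would be too few to develop or test it

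*Protocol article*

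**What the plan says.** All references are to the protocol article.

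- **Outcome measures** gives as the second secondary outcome "the development of a stratification risk system for Type 1 Brugada Syndrome by the integration of ECG Machine Learning algorithms, clinical data and biomarkers". It names the inputs, but no event, endpoint or time horizon.
- **Study design and population** says that prospective-phase data feed the risk algorithm and that the validation phase tests the stratification in a new cohort. For both phases, "enrolment duration will be 24 months and will start during January 2021". Survivors of unexplained cardiac arrest are eligible.
- The same section describes the prospective phase as "a new cohort of 33 patients (11 with spontaneous Type 1 BrS pattern", plus 11 drug-positive and 11 drug-negative patients, with 11 controls. After the sentence on programmed electrical stimulation (PES) in patients with a diagnostic Type 1 pattern, it adds that "after 12 months a final cardiological control examination will be performed".
- For the validation phase, "30 control subjects and 70 subjects (35 spontaneous BrS and 35 suspected), will be enrolled and undergo the same clinical examinations of prospective phase". The Abstract calls the second group of 35 drug-induced rather than suspected.
- **Background** cites annual arrhythmic event rates of "13.5% per year in patients with a history of sudden cardiac arrest" and "3.2% per year in patients with syncope and 1% per year in asymptomatic patients".
- **Trial status** says "The study completion will be in September 2023".

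**The concern.** Two separate matters arise.

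The first is the calendar. The enrolment period and the interval to the final examination add up to more time than the study is given. Followed as written, participants enrolled last reach the completion date without the only follow-up visit the article describes.

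The second is what the risk score may claim. The Background expresses patient risk as arrhythmic events per year, and the validation phase is said to test the stratification. A reader could therefore take the finished score as prognostic evidence in a condition that carries a risk of sudden death. If 12-month events were the yardstick, cohorts of this size would supply almost none. A model combining ECG machine learning, clinical data and transcriptomic markers could be neither fitted nor checked against them.

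**Working it through.** **The plan's own figure.** The article gives no event count or sample size for the risk system. Its only computed figure is 11 per group for the RNA comparison. The usual RNA-seq formula gives n = 2(1.96 + 0.84)² × (1/0.75 + 1) / (ln 6)² = 11.4, close to the stated 11. It has no bearing on this point.

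**Calendar**

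1. Start January 2021, plus 24 months: enrolment ends about December 2022 to January 2023.
2. Plus 12 months: last visits about December 2023 to January 2024, i.e. month 36.
3. Stated completion: September 2023, about month 33.
4. Shortfall: about 3–4 months. The widest reading, 1 September to 31 January, is 5 months.
5. Share affected under uniform accrual (assumed): 3/24 = 12.5% to 4/24 = 16.7%.
6. With 92 patients followed: 92 × 0.125 = 11.5 to 92 × 0.167 = 15.3, or about 12–15. A 5-month gap would give 92 × 5/24 = 19.
7. Person-time lost: those affected lose on average half the shortfall. For 3 months the fraction is (3/24) × (1.5/12) = 1.6%; for 4 months, (4/24) × (2/12) = 2.8%.

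**Number followed.** This is uncertain, because the Abstract and the validation paragraph describe the second 35 patients differently, and the sentence on the 12-month examination does not make clear who has it.

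- 22 + 35 = 57, if only spontaneous patients of the validation cohort count as Type 1
- 22 + 70 = 92, if all 70 count
- 33 + 70 = 103, if the 11 drug-negative patients are also followed

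**Expected arrhythmic events in 12 months** = number followed × annual rate (Background)

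| Patients | 1% (asymptomatic) | 3.2% (syncope) | 13.5% (prior arrest) |
|---|---|---|---|
| 22 (prospective, Type 1) | 0.22 | 0.70 | 2.97 |
| 70 (validation) | 0.70 | 2.24 | 9.45 |
| 57 | 0.57 | 1.82 | 7.70 |
| 92 | 0.92 | 2.94 | 12.42 |
| 103 | 1.03 | 3.30 | 13.91 |

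Each cell assumes that every patient belongs to that risk class. The true mix is not given, so for 92 patients I assumed three (asymptomatic / syncope / arrest):

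- 70/30/0: 92 × 0.0166 = 1.5
- 60/30/10: 92 × 0.0291 = 2.7
- 50/30/20: 92 × 0.0416 = 3.8

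If all the others were asymptomatic, expecting more than 3 events would need over (3/92 − 0.01)/0.125 = 18% arrest survivors, and expecting 10 would need about 79%. Under a Poisson count, the chance of no event at all among 92 is exp(−0.92) = 40% at the 1% rate and exp(−2.94) = 5% at the 3.2% rate.

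**The case against.** The strongest reply is that the article never says the risk system predicts 12-month arrhythmic events. The Background rates are epidemiology, not design assumptions. The 12-month item is an examination and is not described as event ascertainment. Other risk-related information is collected, notably inducibility at PES, and a condensed article may leave the target to the full protocol. This stands. A reader might infer that 12 months of follow-up cannot support the risk-stratification outcome at all; the document does not support that, because the target is unnamed. The unnamed target is not itself the criticism.

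It is also fair that a range of 1–3 events uses only the two lower rates although arrest survivors are eligible, and that the denominator is unsettled. Both points stand, and the counts must be read as conditional. They do not rescue event prediction in the prospective cohort: at the highest rate cited, 22 patients yield about 3 events.

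On the calendar, the reply is that the conflict is small and does not cause the shortage of events. That is right: under uniform accrual it costs about 2–3% of person-time. A reader might also infer that the missed visits would come mostly from the validation cohort, or that data loss is certain. The order of enrolment is not stated, and a wrong date is not proof that visits will be skipped. The contradiction between the stated dates remains.

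**Conclusion.** The date conflict holds on the article's own figures and needs no assumption about case mix; it does need the 12-month examination to apply to patients enrolled at the end of the 24 months, which the shared examination schedule implies for the validation cohort. The shortfall is about 3–4 months. The 12.5–17% of participants affected rests on uniform accrual, and the count of 12–15 also rests on 92 being followed.

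The event shortage holds conditionally. If the risk system is meant to predict arrhythmic events over 12 months, the cited rates give too few to develop or test it: under 1 among the 22 Type 1 patients at 1–3.2% per year, and about 1.5–3.8 among 92 for assumed mixes with 0–20% arrest survivors. The ceiling of 12.4 requires all 92 to be arrest survivors, which is implausible. If another target is intended, this arithmetic says nothing about whether it is feasible.

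The primary outcome, agreement of the ECG model with expert diagnosis, is not affected.

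**What to change.** 1. Move the stated completion date in Trial status to about January 2024, so that every enrolled patient can have the 12-month examination. The cost is 3–4 more months of study. Closing enrolment early instead would, under uniform accrual, give up 18–24 of the 144 planned participants (144 × 3/24 to 144 × 4/24), and the article sets the validation size by what the centres can collect.
2. Add to secondary outcome 2 that arrhythmic events over 12 months are reported descriptively only, and that the risk score is exploratory and not validated against events. The cost is a sentence and a more modest claim; no patients or procedures are added.
3. Make the Abstract and the validation paragraph agree on whether the second group of 35 is drug-induced or suspected, and say who has the 12-month examination.
4. The choice of any other target for the score, such as inducibility at PES, is the sponsor's. The article gives no inducibility rate, so the yield of that target cannot be judged here. Study design and population ties PES to a diagnostic Type 1 pattern, while the PES section refers to spontaneous or suspected patients; these statements must be reconciled.
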